## Discharge from daily clinical monitoring

All patients will receive daily monitoring until they are discharged from the daily monitoring program.

Criteria for discharge are:

1. Ten days post-symptoms onset and 24 hours without fever. Patients meeting these criteria will be discharged from the daily monitoring program. If a patient continues to experience fever more than 10-days post-symptoms onset they will continue to receive daily monitoring until they are fever-free for more than 24 hours.
- OR
2. Patient is hospitalized. Patients that are not hospitalized will continue in the daily monitoring program until criterion #1 is met.

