### 3. Inpatient chart review

Patients with SpO2 <92% or who otherwise are decompensating will be referred back to the triage centers or to a higher level. In these cases, investigators will abstract data on clinical course and patient outcomes from relevant health facilities. A standard data abstraction form will be completed for study subjects who were hospitalized or received outpatient supplemental oxygen in the COVID screening location. Data

collected will include patients' disposition at admission and discharge, treatment received, and length of stay. Each inpatient chart review is estimated to take two hours, including travel time for study staff.

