## Indicators

Specific indicators will be used to assess the feasibility, impact and acceptance of the HBC intervention. Primary outcome indicators are designated with “\*”. Although final indicators may be updated and/or modified, the preliminary set of indicators are listed below.

- Feasibility
  - o Proportion that receive the prescribed HBC intervention
  - o Proportion with complete pulse oximetry data, for relevant arm
  - o Proportion lost to follow-up
- Referral to higher level of care
  - o Proportion referred to higher level care due to hypoxia (i.e. SpO2 < 92%)
  - o Proportion referred to higher level care due to alarm symptoms
  - o Proportion referred to higher level care for any other reason
  - o Proportion referred that reach higher level of care within 24 hours
  - o Proportion who successfully complete HBC without requiring referral
  - o Disposition after referral (home, admission, other) \*
  - o SpO2 level upon arrival to higher level of care
  - o Other clinical measures upon arrival to higher level of care
- Impact on patient outcomes:
  - o Duration of hospitalization (days)\*
  - o Duration of ICU and/or ventilator requirement\*
  - o Mortality\*
- Acceptability
  - o Perception of utility/benefit of strategy (study staff/patients)
  - o Perception of ease of implementation of strategy (study staff)
  - o Changes in hand hygiene behavior

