## Sample size for primary outcome indicators

To calculate the power to detect a difference between two specific groups, we used a two-sided test of independent proportions with the statistical parameters of alpha 0.05, beta 0.2, and power of 0.8. The intervention effect was selected to provide clinically and operationally meaningful outcomes. In addition, the power calculations are based on the following assumptions.

- Likelihood of referral for higher care: According to a study on the use of pulse oximeters to determine referral of COVID-19 patients to a higher level of care, 24.7% of patients required such a referral, in a second study 33% of patients using a pulse oximeter at home and receiving remote COVID-19 management were referred. Given that those studies were conducted prior to the availability of vaccines, and 34% of the Honduran population is vaccinated, we will use a baseline estimate that 20% of patients will be referred for higher care, with a greater proportion referred in the group using pulse oximeters, given additional opportunities to detect the need for referral. The ability to detect a 6% absolute difference between referral rates between arms requires an enrollment of 804 patients per arm for a total enrollment of 1,608 participants.
- Likelihood of hospitalization: The most recent published COVID-19 study in Honduras identified a 25% hospitalization rate in the general population, prior to vaccine availability. We estimate that 10% of all enrolled patients will be hospitalized, taking into account increasing vaccination coverage and the high risk status of the enrolled population. The ability to detect a 5% absolute difference in hospitalization rates between arms requires 946 participants per arm for a total enrollment of 1,892 participants.
- Length of hospitalization: Given an average of 7.7 days hospitalization per admitted patient (SD 10.8), a per arm/strategy sample size of 773 is powered to detect a 20% difference in length of hospitalization between groups for a total enrollment of 1546 participants.
- Pulse oximetry: Given an estimated mean SpO2 of 93% (SD 7%) at the time of evaluation at a higher level of care, a per arm/strategy sample size of 85 is powered to detect an absolute difference between groups of SpO2 of 3%, for a total of 255 patients referred to a higher level of care, for a total enrollment of 850 participants.

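### The starred primary outcome on disposition is defined only among referred patients, yet the protocol expects oximetry to change who is referred, so the arms can differ on it with no effect on admissions

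*Protocol*

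**What the plan says.** The Indicators section states that "Primary outcome indicators are designated with" an asterisk. One starred item, under referral to higher level of care, is "Disposition after referral (home, admission, other". That line is its whole definition. The other starred items are duration of hospitalization, duration of ICU or ventilator need, and mortality. Admission as an event therefore enters the starred list only through disposition after referral.

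Three other places bear on it:

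- **Sample size for primary outcome indicators.** The baseline referral rate is 20%, a greater proportion is expected to be referred in the oximeter group, and 804 per arm is given for a 6-point difference. The same section assumes that 10% of all enrolled patients will be hospitalized and sizes a between-arm comparison of that rate.
- **Indicators.** A separate, unstarred item is "Proportion referred that reach higher level of care within 24 hours", so the protocol foresees that some referred patients will arrive late or not at all.
- **Discharge from daily clinical monitoring.** "Patients that are not hospitalized will continue in the daily monitoring program until criterion #1 is met". A patient sent home after a referral stays under monitoring and can be referred again.

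**The concern.** Referral happens after randomisation, and the oximeter is meant to influence it. An outcome measured only among the referred compares two groups that the intervention itself has selected. If oximetry adds referrals of patients who would not otherwise have been sent, and those patients are mostly not admitted, the share admitted after referral falls in that arm even though no one's admission has changed. Equally, if oximetry raised referrals and admissions in the same proportion, this outcome would show nothing. A difference, or its absence, on this primary outcome therefore cannot be read as the effect of the strategy on admission.

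A second, smaller point concerns coding. A referred patient who never attends could be entered as home or as other, and home also describes a patient who was assessed and released. A patient sent home and then admitted at a later referral has two dispositions, and the line does not say whether the unit is the patient or the referral.

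**Working it through.** **Inputs from the protocol** (Sample size for primary outcome indicators): two-sided alpha 0.05 and power 0.80; baseline referral 20%; difference 6 points, higher with oximeters, hence 26%; 804 per arm; 10% of enrolled patients hospitalized.

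**Step 1. Reproduce the plan's figure.** The method named is a "two-sided test of independent proportions with the statistical parameters of alpha 0.05, beta 0.2, and power of 0.8".

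- Without continuity correction: n = [1.960·√(2·0.23·0.77) + 0.842·√(0.20·0.80 + 0.26·0.74)]² / 0.06² = 771.1, so 772 per arm.
- With continuity correction: (771.1/4)·[1 + √(1 + 4/(771.1·0.06))]² = 804.05, which is 804 to the nearest integer or 805 rounded up.
- A fall from 20% to 14% would give 647 with the correction.

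The stated 804 is therefore the case of 20% v 26%, and the plan is sized for unequal referred groups.

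**Step 2. Size of the referred groups at 804 per arm.** 804 × 0.20 = 160.8, about 161. 804 × 0.26 = 209.0, about 209.

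**Step 3. Admission after referral with no effect on admissions.** Take 10% of enrolled patients admitted in each arm, all through referral: 804 × 0.10 = 80.4 per arm.

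- Phone calls alone: 80.4/160.8 = 0.10/0.20 = 50.0%
- With oximetry: 80.4/209.0 = 0.10/0.26 = 38.5%
- Gap: 11.5 points

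The pooled share is 160.8/369.8 = 0.435 and the standard error is √[0.435·0.565·(1/160.8 + 1/209.0)] = 0.052. So z = 0.115/0.052 = 2.22, two-sided p about 0.026. At these expected counts the artefact alone would pass the 5% level.

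**Step 4. How far this depends on the assumptions.**

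| Assumption varied | Phone calls alone | With oximetry | Gap (points) |
|---|---|---|---|
| Referral 20% v 23%, admission 10% in each arm | 50.0% | 0.10/0.23 = 43.5% | 6.5 |
| Referral 20% v 26%, admission 10% in each arm | 50.0% | 38.5% | 11.5 |
| As the row above, 80% of admissions come through referral | 0.08/0.20 = 40.0% | 0.08/0.26 = 30.8% | 9.2 |
| Referral 20% v 26%, admission 10% v 13% | 50.0% | 0.13/0.26 = 50.0% | 0 |

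The last row shows the reverse error: a 3-point rise in admissions per enrolled patient disappears.

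**Step 5. Non-attendance.** The protocol gives no rate, so the rates here are assumptions, set equal in both arms. At 10%, 20% and 30% of those referred, about 16 v 21, 32 v 42 and 48 v 63 patients have no facility disposition. The excess with oximetry, about 5 to 14 patients, comes only from the larger number referred.

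**Step 6. The same case over everyone randomised.** 80.4/804 = 10% in each arm, gap 0. With 13% admitted under oximetry the gap is 3 points, which is the true effect.

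**The case against.** The strongest reply is that first, last or worst disposition, patient or referral as the unit, and the coding of non-attenders are derivation rules that a protocol commonly leaves to the SAP, which is not at hand. The list is also provisional: "Although final indicators may be updated and/or modified". This stands. Silence on those rules is not an error in the protocol. The choice of referred patients as the population of a primary outcome is different, because it is in the text and coding rules would not undo it.

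A second reply is that admission over all enrolled patients is already planned, since the sample size section powers it. This stands in part. It shows that the sounder contrast is intended, but the starred list does not contain it and stars the conditional outcome instead.

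A reader might go further in three ways that the document does not support:

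- **That non-attenders are counted as home.** The text does not say so. The undefined category other could hold them, and attendance has its own indicator. Under Inpatient chart review, "investigators will abstract data on clinical course and patient outcomes from relevant health facilities", so disposition may be meant as the facility's decision. The classification is ambiguous, not wrong.
- **That oximetry makes non-attendance or repeat referral more common.** The protocol predicts more referrals, not a different rate of either. A patient referred on a reading without feeling ill might attend less, or a visible low reading might prompt attendance.
- **That recoding non-attenders would remove a spurious difference in admission.** It would not. The share admitted among the referred is the same whatever label the non-attenders carry. Only a change of denominator removes the artefact.

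**Conclusion.** The point holds for the denominator. On the plan's own referral rates, and with the same 10% of enrolled patients admitted in each arm through referral, the starred outcome would show 50.0% v 38.5% admitted, a gap of 11.5 points with no effect on admissions. The gap shrinks if referral differs by less than 6 points or if some admissions bypass referral, and it vanishes if oximetry does not change the referral rate. It needs no assumption about attendance or repeat referral.

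The ambiguity over non-attenders and repeat referrals is real but secondary. An SAP may already settle it, and the size or direction of any arm difference on those paths is unknown. The change should be made because the outcome is primary and the remedy is cheap. It does not call the other starred outcomes or the design into question.

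**What to change.** For the between-arm contrast, redefine the indicator as disposition over the whole monitoring period, scored once per randomised participant, with all randomised participants as the denominator. Use unranked categories: never referred; referred, did not attend; assessed and sent home; oxygen without admission; admitted; died. Leave them unranked, because non-attendance is neither a milder nor a worse clinical result than being assessed and released.

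Take the proportion admitted as the main contrast, counting anyone admitted at any point. That contrast does not depend on how repeat referrals are placed in the other categories, and it agrees with the all-enrolled hospitalization rate that the sample size section already powers. Report disposition among the referred as descriptive only, by arm, with no claim about effect.

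Confirm that the forms record whether a referred patient attended. Under Inpatient chart review, "A standard data abstraction form will be completed for study subjects who were hospitalized or received outpatient supplemental oxygen", so that form alone would not identify a patient who never went or who was sent home without oxygen. The daily call form is not shown and may already hold this, since the 24-hour indicator needs it. If it does not, one item should be added.

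The cost is a change of indicator wording and at most one form item. The downside is six categories in place of three, some of them sparse.

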## Background

As of December 16, 2021, there have been more than 271 million confirmed cases of COVID-19 and 5.3 million deaths worldwide. Secretary General of the United Nations Antonio Guterres has stated that the impact of the COVID-19 pandemic has fallen “disproportionately on the most vulnerable: people living in poverty, the working poor, women and children, persons with disabilities, and other marginalized groups.” In Honduras, as of April 12th, 2021, there had been 378,642 confirmed cases of COVID-19, leading to 10,424 deaths.

While most COVID-19 patients have mild or moderate symptoms, some individuals develop serious or critical signs and symptoms. Persons with marked hypoxia may have normal respiratory rates but later develop severe symptoms or respiratory failure. Timely detection and transfer of persons with hypoxia or other alarm signs and symptoms to a higher level of care is critical.

According to the WHO, “home pulse oximetry is a safe, non-invasive way to assess oxygen saturation in the blood and can support the early identification of low oxygen levels in a patient with initially mild or moderate COVID-19 or silent hypoxia, when a patient does not appear to be short of breath but his or her oxygen levels are lower than expected.” Pulse oximetry can also identify patients for whom it is safe to remain in HBC, thereby reducing unnecessary use of advanced care resources, which are frequently limited. There is currently limited evidence on the impact, feasibility, and acceptability of home-based pulse oximetry in resource-limited settings.

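### Length of stay per admitted patient is starred as a patient-impact outcome, but the oximeter is meant to change both when and how often patients are referred, so a difference between arms cannot be read as benefit or harm

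*Protocol*

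**What the plan says.** The protocol's Indicators section states that "Primary outcome indicators are designated with" a star. In its group on impact on patient outcomes it stars "Duration of hospitalization (days", next to ICU or ventilator duration and mortality. No start point is written out.

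The section on sample size for primary outcome indicators shows how the stay is conceived: "Given an average of 7.7 days hospitalization per admitted patient (SD 10.8". It adds that "a per arm/strategy sample size of 773 is powered to detect a 20% difference in length of hospitalization between groups". The inpatient chart review abstracts length of stay from the records of patients who were hospitalized or received outpatient oxygen. Taken together, the measure is admission to discharge among those admitted.

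The Background gives the reason for the oximeter: it "can support the early identification of low oxygen levels in a patient with initially mild or moderate COVID-19 or silent hypoxia". Under Home-based care strategies, only Strategy 2 takes saturation readings, up to four a day. The sample-size section expects more referrals in that arm because there are more chances to detect the need.

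**The concern.** A stay counted from admission starts on a date that the intervention is designed to move. A patient in the oximeter arm who is admitted a day earlier and goes home on the same date scores one day more. Under a patient-impact label, that reads as a worse outcome.

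The intervention is also expected to change who is referred. If that brings in patients who would otherwise have stayed at home, the two arms' admitted groups are no longer comparable, and randomisation does not protect a comparison between them. Adding milder, shorter stays lowers the oximeter arm's mean and reads as benefit, even if nobody has recovered faster.

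At stake is a starred result that bears on Objective 3, the impact of oximetry on outcomes, and that is meant to inform ministry policy. It could point either way for reasons unrelated to how patients fare.

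**Working it through.** **Inputs from the protocol (sample size section).** Mean stay 7.7 days and SD 10.8 per admitted patient; 20% difference; 773 per arm; "alpha 0.05, beta 0.2, and power of 0.8". The section names a "two-sided test of independent proportions", so two-sided is carried over to the comparison of means. Share admitted: "We estimate that 10% of all enrolled patients will be hospitalized". Largest stated enrollment: 946 per arm, for hospitalization.

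**Assumptions not in the protocol.** The lead time L (how much earlier admission occurs, averaged over the oximeter patients who would be admitted under either strategy); the extra proportion admitted, e; and the mean stay s of those extra patients.

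**Step 1. Reproduce the protocol's figure.** The difference is 0.20 × 7.7 = 1.54 days.
n per arm = 2 × (1.960 + 0.842)² × 10.8² / 1.54² ≈ 772.1, rounded up to 773. This matches.

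**Step 2. Lead time alone.** With the same patients admitted and the discharge date unchanged, the oximeter mean is 7.7 + L. The chance of a significantly longer stay is Φ(L / SE − 1.96), with SE = 10.8 × √(2/n) and n the number of stays per arm. At 10% hospitalization, 773 enrolled give 77 stays and 946 give 95.

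| L (days) | Rise in mean stay | 773 stays per arm | 77 stays | 95 stays |
|---|---|---|---|---|
| 0.5 | 6.5% | 15% | 5% | 5% |
| 1.0 | 13.0% | 44% | 8% | 9% |
| 1.54 | 20.0% | 80% | 14% | 16% |
| 2.0 | 26.0% | 95% | 21% | 25% |

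For L = 1.54 and 77 stays: SE = 10.8 × √(2/77) = 1.74, L / SE = 0.885, and Φ(−1.075) = 0.14.

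**Step 3. Add a change in who is admitted.** Let 10% be admitted in the comparison arm. In the oximeter arm the same 10% stay 7.7 + L days, and an extra proportion e stays s days.
Mean = [0.10 × (7.7 + L) + e × s] / (0.10 + e).

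| L | e | s | Oximeter mean | Difference from 7.7 |
|---|---|---|---|---|
| 0 | 5% | 3 | 6.13 | −1.57 |
| 1 | 5% | 3 | 6.80 | −0.90 |
| 1 | 2% | 3 | 7.75 | +0.05 |
| 2 | 5% | 5 | 8.13 | +0.43 |
| 2 | 2% | 3 | 8.58 | +0.88 |

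The effects cancel when s = 7.7 − 0.10 × L / e. For L = 1 that is 5.7 days at e = 5% and 2.7 days at e = 2%. The first row shows that extra short stays alone, with no lead time, can produce an apparent gain as large as the design difference.

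**Step 4. The same case on two scales.** Take L = 1, e = 5%, s = 3. Per admitted patient, the oximeter arm looks better by 0.90 days. Per randomised participant, hospital days rise from 0.10 × 7.7 = 0.77 to 0.10 × 8.7 + 0.05 × 3 = 1.02, an increase of 0.25. Conditioning on admission reverses the sign.

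Death early in a stay also shortens it. Whichever arm has more such deaths gains on this measure.

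**The case against.** The best defence is that an earlier admission with an unchanged discharge date does put the patient in hospital for longer. That is a true effect of the strategy and is relevant to resource utilization, Objective 4. This stands. The number is valid as resource use; the fault lies in starring it as patient impact.

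Second, no lead time is given, and a long average lead may be implausible. Both arms receive daily calls that check for alarm signs, and some referrals will be for reasons to which the oximeter adds nothing. An unchanged discharge date is also an assumption, since the protocol hopes that timely transfer helps. This too stands, so the lead-time figures are a range and not a prediction.

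Third, the protocol calls its indicators preliminary, the start of the clock is inferred from the per-admitted-patient sizing and the chart abstraction, and the SAP was not available. But the protocol itself makes the outcome primary, labels it patient impact and sizes it per admitted patient, and an SAP that follows it inherits the problem. Its covariate adjustment cannot move an admission date or restore comparability of the admitted groups. Saturation on arrival, also an indicator, could reveal earlier presentation but would not correct for it.

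Two stronger readings are tempting. A reader might infer that the oximeter arm will look worse. The documents do not support that: the protocol expects more referrals in that arm, and the third step shows either sign. A reader might also infer an 80% chance of a falsely significant longer stay. That needs 773 admitted patients per arm, whereas the protocol gives 773 as enrollment and expects 10% to be hospitalized.

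**Conclusion.** The point holds as a fault in how a primary outcome is classified and conditioned. Both the start of the stay and membership of the admitted group can depend on the arm, so the starred comparison cannot be read as patient benefit or harm. Each day of lead adds 13% to the mean stay, and 1.54 days equals the full design difference. An extra 5% admitted for 3 days each would move the mean by about as much in the opposite direction. The net direction is undetermined.

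These sizes rest on an assumed lead time, an assumed unchanged discharge date, and assumed numbers and lengths of extra stays. With about 77 to 95 stays per arm, a 1.54-day lead alone would reach significance about 14 to 16% of the time, so the main harm is an uninterpretable estimate and not a likely false positive. Mortality, also starred, has no admission clock and is unaffected.

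**What to change.** Move admission-to-discharge days out of the patient-impact group and report them as a resource-use indicator under Objective 4.

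For patient impact, compare all randomised participants from enrollment over one fixed window of stated length, with death given the worst score. Days alive and out of hospital is one example. State in the text that this removes the selection on admission but still counts the real extra hospital days that earlier admission causes: a one-day lead in 10% of participants costs 0.10 day per participant. Read it beside mortality.

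A score of zero for those never admitted and otherwise days from enrollment to discharge alive should not be used instead. It leaves deaths without a score, and a one-day admission on day 8 would count as about nine days.

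The cost is wording plus two practical items. The 7.7-day (SD 10.8) calculation no longer applies and the sample size must be restated for the new outcome. The chart abstraction form must capture admission and discharge dates, since the protocol lists only disposition, treatment and length of stay. Readmissions and deaths within the window also have to be found. Hospitalized patients leave daily monitoring and the later surveys are optional, so the planned linkage to ministry records through the national identification number would have to serve.

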### Objectives

- 1) To support and strengthen existing HBC for higher risk COVID-19 patients in Honduras
- 2) To generate operationally relevant data to provide the Honduras SESAL and other health authorities with HBC guidance and protocols.
- 3) To assess the utility and impact of pulse oximetry on outcomes for HBC.
- 4) To evaluate differences in resource utilization by HBC strategy.
- 5) To assess acceptability of different HBC strategies by patients, study staff, and SESAL clinicians staffing triage centers.
- 6) To assess the prevalence of post COVID-19 conditions.
- 7) To assess participant-reported in-home hand hygiene practices before and after receiving HBC kit.
- 8) To assess if participants with access to alcohol-based hand sanitizer (ABHS) practice hand hygiene more frequently.
- 9) To evaluate preferences for different hand hygiene technologies.

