## Data collection and survey tools

### 1. Enrollment questionnaire

All enrolled patients will complete an enrollment questionnaire that will include demographic and clinical information, risk factors, hand hygiene practices and other WASH variables, and socio-behavioral questions.

Questions will include timing and nature of symptoms, and COVID-19 compatible symptoms, if anyone else in the household has had COVID-19 symptoms in the past 30 days, and if so, when they began and how long they lasted. In order to later link patients with COVID testing results and follow-up visits to the CETTE or hospital in a SESAL database, we will also collect the patient's national identification number, but a unique study identification number will also be assigned. The enrollment questionnaire will also assess risk factors of the participant and household members such as which household members leave the house for work or school and if there are any other possible exposures to COVID-19. Specific questions about the WASH component include assessing the participants' knowledge, attitudes, and practices about hand hygiene in the month prior to visiting the triage center. The enrollment questionnaire will assess access to hand hygiene resources in the participants' homes. The estimated time to complete enrollment and questionnaire is 20-25 minutes.

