#### **4. Follow-up hand hygiene assessment**

Serial follow-up WASH survey will be administered every week and at discharge (from acute COVID-19 daily monitoring) during the daily follow-up phone calls for the HBC study. The follow-up hand hygiene assessment will repeat questions about participant-reported in-home hand hygiene practices. The follow-up questionnaire may also assess the safe usage of the ABHS in the home by asking if there have been any adverse events (e.g. splash in eye or ingestion). This questionnaire is estimated to take 5 minutes. Additionally, to understand behavioral and preferential aspects of different hand hygiene technologies, upon discharge from the period of acute monitoring, 10 patients from each ABHS arm will be selected to complete Hand-Hygiene In-depth Interviews which are estimated to take 5-10 minutes. All patients enrolled in the study are eligible for selection for interviews. The 10 patients will be selected as a convenience sample based on availability of study staff.

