## Data analysis

The primary analysis will provide unadjusted and adjusted differences between arms/strategies based on the covariates listed. We will perform additional subgroups analyses, specifically examining age, sex, comorbidities, baseline clinical features, and timing of the interventions. Qualitative analyses will be conducted by trained researchers using Excel to organize data, given the limited sample sizes. Research analysis will adhere to the Sex and Gender Equity in Research (SAGER) guidelines including reporting representativeness, presenting disaggregated results regardless of positive or negative outcome, withdrawal/attrition rates, and implications of reported gender on study results.

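### The hand sanitizer objective asks about frequency between groups, but the only hand-hygiene indicator is a change and the listed covariates omit the baseline practice already collected

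*Protocol*

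**What the plan says.** Two objectives concern reported practice. Objective 7 is a before-and-after description in all participants: "To assess participant-reported in-home hand hygiene practices before and after receiving HBC kit". Objective 8 compares groups: "To assess if participants with access to alcohol-based hand sanitizer (ABHS) practice hand hygiene more frequently".

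The data for both are collected. The enrolment questionnaire covers "practices about hand hygiene in the month prior to visiting the triage center". Afterwards, "Serial follow-up WASH survey will be administered every week and at discharge", and "The follow-up hand hygiene assessment will repeat questions about participant-reported in-home hand hygiene practices". No recall window is given for the follow-up questions.

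In the Indicators section the only hand-hygiene entry is "Changes in hand hygiene behavior". It stands under Acceptability, without the asterisk that marks a primary indicator, and has no scale, time point or summary measure. The list itself is provisional: "Although final indicators may be updated and/or modified, the preliminary set of indicators are listed below".

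The Data analysis section says: "The primary analysis will provide unadjusted and adjusted differences between arms/strategies based on the covariates listed". The only table with a column headed Covariate closes the sample size section. Its three rows are the proportion hospitalised, the duration of hospitalisation, and SpO2 on evaluation at a higher level of care. Hand hygiene at enrolment is not among them.

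**The concern.** The named indicator fits objective 7 and does not express objective 8. A reader who wants to analyse the ABHS comparison from the protocol has two literal options: compare changes from enrolment, or compare follow-up values with a covariate set that leaves out the enrolment value. Each makes poorer use of the baseline than regression of the follow-up value on group and baseline.

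A change score fixes the baseline slope at 1, and a follow-up-only comparison fixes it at 0. With equal variances the best slope is rho, the correlation between the two measurements. If the groups differ by chance by D at baseline, the change score over-corrects and leaves an error of −(1−rho)D, while the follow-up comparison leaves +rho·D. These errors average to zero over repeated random allocation, so they cost precision and do not add bias.

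What is at stake is the precision of a secondary comparison, for which the needed data are already in hand.

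**Working it through.** **Inputs.** The protocol gives no sample size, SD, effect, correlation or item scale for hand hygiene, so there is no figure of its own to reproduce. Assumed: a continuous score, SD 1 at both times, rho of 0.3, 0.5 or 0.7, and independent participants (the allocation of ABHS by day of the week is ignored). Two-sided alpha of 0.05 and power of 0.80 are borrowed from the sample size section, where they apply to primary indicators.

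**Variances, relative to follow-up only (= 1).**
- Change score: 2(1−rho)
- Baseline-adjusted (ANCOVA): 1−rho²
- ANCOVA relative to change: (1−rho²)/[2(1−rho)] = (1+rho)/2

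| Assumed rho | Change | ANCOVA | ANCOVA/change | N for change ÷ N for ANCOVA, 2/(1+rho) |
|---|---|---|---|---|
| 0.3 | 1.40 | 0.91 | 0.65 | 1.54 |
| 0.5 | 1.00 | 0.75 | 0.75 | 1.33 |
| 0.7 | 0.60 | 0.51 | 0.85 | 1.18 |

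**In terms of power.** An analysis with 80% power has a standardised effect of 1.960 + 0.842 = 2.802. Where ANCOVA has 80%, the change score has Φ(2.802 × √[(1+rho)/2] − 1.96):
- rho 0.3: Φ(2.259 − 1.96) = 62%
- rho 0.5: Φ(2.427 − 1.96) = 68%
- rho 0.7: Φ(2.583 − 1.96) = 73%

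Where follow-up only has 80%, ANCOVA has Φ(2.802/√(1−rho²) − 1.96), which is 84%, 90% and 97.5% at the same values.

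The change score is not always the weakest choice. Its variance 2(1−rho) exceeds that of follow-up only for rho below 0.5 and is smaller above it.

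**Recall windows.** Suppose the one-month enrolment question shifts every baseline answer by s in both groups. The difference in mean change is then (Y1 − B1 − s) − (Y0 − B0 − s), and s cancels. A simulation confirms this, with 804 per group (the referral figure, used only for illustration), rho 0.5, a true difference of 0.10 SD and a common shift of 2 SD:

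| Baseline SD | Mean estimate, change | Mean estimate, ANCOVA | Power, change | Power, ANCOVA |
|---|---|---|---|---|
| 1.0 | 0.102 | 0.102 | 53% | 64% |
| 1.5 | 0.099 | 0.099 | 33% | 64% |

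Both estimates stay on target. A baseline on a wider scale makes the change score noisier: its variance becomes 1 + 2.25 − 2(0.5)(1.5) = 1.75 instead of 1. ANCOVA is unaffected because it estimates the slope. The shift does go straight into a within-person before-and-after difference, so it matters for objective 7.

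**The case against.** The strongest reply is that the protocol does not prescribe a change-score test of ABHS at all. The indicator is a short label in a list declared preliminary. It reads naturally as the measure for objective 7, while objective 8 is worded as frequency. The sentence in Data analysis is about the primary analysis, and hand hygiene is not a primary indicator. The table headed Covariate sits in the section on sample size for primary outcomes, with a column of general-population values, and looks like planning inputs. Nothing rules out baseline adjustment, and the choice of model for a secondary comparison is commonly left to a statistical analysis plan.

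Most of this stands. A reader might infer that the plan commits itself to change scores, that objective 8 therefore loses a known amount of power, and that the unlike recall periods distort the ABHS comparison. The documents support none of these: no such commitment is made, no input exists from which to compute a loss, the follow-up recall window is not stated, and a mismatch shared by both groups cancels.

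What remains is narrower. The protocol names an outcome for hand hygiene, and that outcome does not match objective 8. It also refers to a covariate list, and the list lacks the one baseline variable that is plainly relevant. The Data analysis sentence speaks of arms as well as strategies, and the protocol calls the ABHS groups arms elsewhere, so a reader may apply it to the ABHS comparison. Even if it does not apply, no other quantitative analysis of that comparison is described.

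**Conclusion.** The point holds as a minor, cost-free improvement to a secondary indicator. It is not an error that biases a result. Analysing ABHS on change, or on follow-up without the enrolment value, would be less precise than the collected data allow. The variance ratios of 0.65 to 0.85 (against change) and 0.91 to 0.51 (against follow-up only) for rho from 0.3 to 0.7 are illustrations. They rest on an assumed rho, a continuous score, equal variances and independent participants. For categorical items they are only a rough guide. The loss in this trial cannot be stated. Any difference in recall windows mainly affects the before-and-after description under objective 7.

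**What to change.** In Indicators, add an entry for objective 8: reported hand-hygiene practice at a named follow-up time (one of the weekly surveys or discharge), ABHS versus no ABHS, adjusted for the same practice at enrolment. In Data analysis, add one sentence: ANCOVA for frequency scores, and logistic or ordinal regression with the enrolment response as a covariate for categorical items. Keep the raw before-and-after change as a description for objective 7, and state the recall window of the follow-up questions so that this description can be interpreted.

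The cost is a few sentences. No new data, visits or participant time are needed, and because the indicator list is declared open to modification, the change fits the protocol as written.
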